### Blinding

The study will have a double-blind design to improve the reliability of results. Random distribution of participants to groups will be supervised by an external investigator, who will use computer-generated numbers to encode the assignment of patients to intervention groups; thus, neither the neurologist nor the evaluator(s) will know which group a patient is in. The study aims to achieve allocation concealment by recording the patients’ randomized group assignments in sealed envelopes, with the researchers and patients having no control over the random allocations, and ensuring that no one involved in the study is aware of the treatment allocations. After the patient signs the informed consent form, an envelope will be opened, and treatment will be allocated in a coded form. Patients will be randomly allocated into two groups, namely, active iTBS and sham stimulation, in a 1:1 ratio. Group allocation will be communicated via email to the person responsible for applying the iTBS treatment. This person will not take part in the data analysis or in the post-iTBS evaluation. All patients will be naive to TMS, and the patients will be kept blind to their assigned treatments throughout the process.

### Procedure and intervention

Our study will be composed of 2 different phases, Phase I and Phase II, separated by a washout period of at least 3 months. Each phase will consist of 3 stages: baseline evaluation, iTBS intervention, and posttreatment evaluation (Figure 1). The baseline evaluation period will begin once the patients agree to participate in the investigation. From this moment until a maximum of 30 days later, patients will undergo (i) a clinical and motor examination in the ON state, (ii) an extensive cognitive and neuropsychiatric assessment, (iii) a resting-state EEG recording, (iv) structural and functional MRI scans, and (v) blood sample collection. Moreover, immediately following the completion of baseline evaluations and just prior to the start of the iTBS intervention stage, a variety of TMS-EMG cortical excitability measures will be acquired. Once this first stage is fully completed, patients will receive a session of real or sham iTBS over the bilateral M1 once per day for five consecutive days. During the last session of iTBS, TMS-EMG parameters of cortical excitability will be acquired, and patients will undergo a clinical motor evaluation. After the intervention stage, the posttreatment evaluations will be conducted. Subsequently, within a 3–4 day window, resting-state EEG data will be recorded for all participants. A week after the last iTBS session, patients will undergo a second clinical evaluation, and a new blood sample will be collected. Next, on the eighth day posttreatment, structural and functional MRI scans will be acquired. At 2 weeks post-iTBS, a new neuropsychiatric and cognitive assessment will be performed along with a third motor evaluation. Finally, the last visit will occur 28 days after the iTBS intervention, consisting of the fourth and final clinical evaluation (Figure 1). Subsequently, all patients will undergo a washout period of at least 3 months prior to the start of the crossover process and Phase II of the study.

**Figure 1 fig1:**
[figure not shown]
Flowchart of the study design.

As this study was designed to have a duration of 26 months, the scheduling of all patients will be staggered. According to our schedule, the patient screening period is expected to be completed by month 18. Protocol implementation is expected to be completed by month 30.

#### TMS intervention and neuronavigation

TMS pulses and the iTBS protocol will be delivered using a Magstim Rapid^2^ Magnetic Stimulator (Magstim, Whitland, United Kingdom) connected to a 70 mm air-cooled figure-eight coil (AirFilm® Coil, Magstim, Whitland, United Kingdom). The iTBS treatment will be applied on the motor hand area; real iTBS will have the following parameters: 3-pulse bursts at 50 Hz repeated every 200 ms and delivered as short trains of 10 bursts lasting 2 s and an intertrain silence period of 8 s, for a total of 600 pulses (20 cycles of trains) and a total duration of 190 s. During the five-day iTBS intervention stage, one iTBS session per day will be conducted, with iTBS administered to the bilateral M1 at 80% of the active motor threshold (aMT) in the real condition. Primarily, although the majority of the PD patients are usually bilaterally affected, real or sham iTBS interventions will always start in the M1 contralateral to the most clinically affected hemibody as determined by the MDS-UPDRS-III baseline score. Protocol intensity will be determined on the first day of the intervention and maintained until the last session. The same coil and device will be used for excitability parameter acquisition and iTBS. Sham stimulation during treatment will follow the same procedure except it will be performed with an AirFilm® SHAM coil (Magstim, Whitland, United Kingdom). Both coils are identical in appearance and produce a similar sound and sensation, although the sham coil delivers no stimulation.

Before the iTBS sessions, a full brain and head 3D curvilinear reconstruction will be obtained using a high-resolution 3D T1-weighted anatomical image for neuronavigation (Brainsight, Rogue Research). The T1-weighted image will be rotated and reoriented to the anterior and posterior commissure (AC-PC) plane. Coregistration of the subject to the images will be performed by using four anatomical landmarks: the bridge of the nose, tip of the nose, left preauricular area (LPA) and right preauricular area (RPA). The coil will be placed tangentially to the scalp, and the handle of the coil will be pointing backward and tilted away from the midline of the central sulcus at a 45° angle (Groppa et al., 2012), inducing an anterior–posterior/posterior–anterior current over the bilateral motor hand area, traditionally referred to as the “hand-knob” and corresponding to an inverted omega or epsilon shaped-structure (in the axial plane) located at the middle genu of the central sulcus in the precentral gyrus (Yousry, 1997; Sparing et al., 2008). Because of its large motor cortex representation and low motor unit-to-muscle fiber innervation ratio, the first dorsal interosseous (FDI) muscle of the hand was chosen to quantify TMS-related motor evoked potentials (MEPs; Palmer and Ashby, 1992; Chaves et al., 2021). The optimal position for stimulation will be found by neuronavigated cortical mapping at the time that FDI muscle activation is observed via visual feedback from the electromyography devices and visual inspection. Subsequently, the resting motor threshold (rMT) and aMT, as well as the cortical silent period (cSP) and “20 trials” (20 t), will be determined for the FDI muscle. Again, acquisition of TMS-derived measures of cortical excitability will always be started in the most affected hemisphere (for a more detailed description of the definition and measurement of cortical excitability parameters used in our study, see *Data Collection & Analysis* and *TMS-derived measures of cortical excitability*).

Motor mapping will be performed on a 3 × 3 mm grid above the motor hand area. The center of the grid will be located on the central point of the hand-knob structure such that this area and possible error range are fully covered. For hotspot identification, the central point of the grid will be used for the determination of the minimum suprathreshold intensity that elicits a peak-to-peak MEP > 50 μV for three consecutive trials in the resting state. Subsequently, one TMS pulse will be given at each spot of the grid at 110% of this established intensity. The optimal location or hotspot will be determined as the grid position with the largest amplitude and the shortest latency that provokes movement in the FDI muscle. If these two parameters are not in the same spot, the optimal location will be defined according to the largest amplitude (Charalambous et al., 2019). If no neuroimaging images are available or hotspot identification is not successful after grid mapping, the 10/20 system C1/C2 will be used to locate the motor hand area, which has been demonstrated to offer a more accurate position for the motor hand area than C3/C4 (Silva et al., 2021; Kim et al., 2023). Visually guided and neuronavigated manual mapping will be performed to identify the location of the FDI muscle hotspot. This process will be replicated for both hemispheres.

### Outcome measures

Participants will undergo an extensive assessment of seven areas of interest: basic demographic information, clinical and motor assessment, TMS-EMG parameters of cortical excitability, cognitive and neuropsychiatric evaluations, electrophysiology and neuroimaging examination, and serum biomarker testing. Each measure will be collected before and after treatment for both the real and sham groups and during the two phases of the study. Primary, secondary, and exploratory outcome measures are summarized in the Table 1.

**Table 1 tab1:** Primary, secondary, and exploratory outcome measures.

	Measure	Domain measured
**Primary outcomes**		
Clinical improvement	MDS-UPDRS (part II, III, IV)	Severity and progression of PD symptoms

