## Abstract

**Background and objectives:**

Intermittent theta-burst stimulation (iTBS) is a patterned form of excitatory transcranial magnetic stimulation that has yielded encouraging results as an adjunctive therapeutic option to alleviate the emergence of clinical deficits in Parkinson’s disease (PD) patients. Although it has been demonstrated that iTBS influences dopamine-dependent corticostriatal plasticity, little research has examined the neurobiological mechanisms underlying iTBS-induced clinical enhancement. Here, our primary goal is to verify whether iTBS bilaterally delivered over the primary motor cortex (M1) is effective as an add-on treatment at reducing scores for both motor functional impairment and nonmotor symptoms in PD. We hypothesize that these clinical improvements following bilateral M1-iTBS could be driven by endogenous dopamine release, which may rebalance cortical excitability and restore compensatory striatal volume changes, resulting in increased striato-cortico-cerebellar functional connectivity and positively impacting neuroglia and neuroplasticity.

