### Recruitment and sample size

The recruitment period will last approximately one and a half years. During this time, we plan to enroll 24 PD patients who meet the inclusion and exclusion criteria. Recruitment will be entirely managed by neurologists from the Movement Disorders Unit at the Puerta del Mar University Hospital. Every candidate patient will undergo a clinical review by a neurologist specializing in movement disorders, who will assess the suitability of each patient for inclusion in this study.

The inclusion criteria for patients will be as follows: (i) diagnosed with PD according to the United Kingdom Parkinson’s Disease Society Brain Bank diagnostic criteria (UK PDSBB; Gibb and Lees, 1988); (ii) disease duration of at least 5 years to reduce the risk of including levodopa-responsive atypical Parkinsonism patients (Lang et al., 2006; Tolosa et al., 2006; Mestre et al., 2014); (iii) disease symptomatology in the ON medication state at a Hoehn y Yahr (H&Y) scale of II–III; (iv) clinical and therapeutic stability in the last 2 months previous to the recruitment period; and (v) aged 45–75 years.

The exclusion criteria will be as follows: (i) lack of a PD diagnosis that meets the UK PDSBB diagnostic criteria; (ii) presence of a serious systemic disease; (iii) presence of severe or moderate cognitive impairment comparable to dementia as indicated by a Mini-Mental Parkinson (MMP) score of ≤24; (iv) any incapacitating psychiatric or other clinical condition that might affect the correct performance of this protocol, such as any dystonia and/or dyskinesia; (v) receipt of amantadine within the previous 60 days; and (vi) any sign of atypical parkinsonism, neurological comorbidities, or history of cranioencephalic traumatism or epilepsy or any other contraindication to neurostimulation with TMS (e.g., magnetic intracranial implant, cardiac pacemaker).

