The few TMS or TBS studies using a crossover design (Eggers et al., 2010; Maruo et al., 2013; Bologna et al., 2015; Kim et al., 2015; Vanbellingen et al., 2016; Yokoe et al., 2018; Hill et al., 2020; Brugger et al., 2021) have demonstrated the favorable efficacy of high-frequency rTMS over the M1 on motor symptoms in PD (compared to sham stimulation). The necessary sample size was calculated based on the primary endpoint, i.e., the motor clinical changes as assessed by the UPDRS-III score. Considering these findings and the statistical parameters needed to detect a treatment difference for a 2 × 2 crossover study at a two-tailed *p* value of 0.05 and a power of 80%, the total sample size was calculated to be at least 21 subjects. With an assumed drop-out rate of approximately 20%, we estimated a final minimum sample size of 24 patients.

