### Statistical analysis

Before any statistical analyses are performed, the normality of the data distributions of outcome variables and parameters will be assessed using the Shapiro–Wilk test to determine whether parametric or nonparametric statistical tests should be used for the different measures in this study. Subjects will act as their own controls, and the data will be analyzed using both parametric (independent-samples *t*-test) and nonparametric (Mann–Whitney U test) methods, as appropriate. To evaluate the carryover effects, a preliminary test will be performed to test the assumption that the washout phase lasted long enough to completely eliminate a carryover impact. To do this, an independent-samples test will be used to compare the sum of the values measured in the two periods for each subject across the two sequence groups.

In the first step, exploratory analysis of correlations between the clinical response variables and all outcome measures will be conducted. Primarily, correlation analyses will be applied to examine correlations of TMS-EMG parameters with motor, clinical, and neurocognitive variables as well as serum biomarkers and brain structural and functional variables. In a second step, significant correlations across timepoints (i.e., use of baseline variables to predict the clinical response at posttreatment) will be analyzed using stepwise multiple regression models to identify the potential factors predicting the clinical response after iTBS.

For structural MRI and functional (EEG, fMRI) data, individual analysis will first involve the statistical pipeline of each software or toolbox (e.g., SPM12, Fieldtrip, Brainstorm, etc.). Next, advanced statistical analysis will be performed by incorporating clinical, cognitive, neuropsychiatric, serum biomarker, electrophysiological, and neuroimaging information using SPSS 23.0 (IBM, Chicago, IL, United States), R, and custom routines written in MATLAB (MathWorks, Natick, United States). Issues affecting the risk of bias related to missing data in our crossover study will be considered. Initially, all patients with missing outcome data will be removed from the analysis of each data subset. Other strategies for managing missing data, such as the last observation carried forward, will also be used to impute values. The threshold for statistical significance will initially be set at *p* < 0.05. All statistical tests will be two-tailed and adjusted for multiple comparisons.

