While it has been demonstrated that a few sessions of rTMS or TBS can increase GM volume at the stimulation site as well as in more distal brain regions (May et al., 2007), the potential role of cerebral CT as a possible biomarker of iTBS treatment response in PD patients still needs to be assessed. These GM volume changes could demonstrate the substantial neuroprotective effects of rTMS or TBS, likely dependent on a wide range of micro- and macroscopic neural mechanisms (Ji et al., 2021; Jung and Lambon Ralph, 2021). In light of this, metabolic neuroimaging studies have provided additional evidence of neuroplastic changes after rTMS or TBS, as M1 rTMS was shown to influence the resting-state activity of the motor system after the stimulation had ended as well as in brain regions connected to the stimulation site (Lee et al., 2003; Rounis et al., 2005), demonstrating an acute reorganization of activity to other areas. Moreover, studies in PD patients have reported changes in functional connectivity between the M1 and basal ganglia or between the prefrontal areas and the SMA after low-frequency (Wang et al., 2023) or high-frequency rTMS (González-García et al., 2011), respectively. Despite the evidence demonstrating altered brain functional connectivity in PD, conclusive data regarding the potential link between clinical improvement and changes in the brain’s structural and functional connectivity after iTBS in these patients are lacking.

In conclusion, this study is designed to provide new insights that promise to advance our understanding of the efficacy of M1-iTBS in improving symptomatology in the early and middle stages of PD. We hypothesize that bilateral M1-iTBS will considerably improve motor functioning in PD patients, as measured by MDS-UPDRS parts II, III, and IV, in addition to alleviating nonmotor symptoms. A growing body of evidence from preclinical and human studies allows us to further hypothesize that the striatal endogenous dopamine release triggered by iTBS may rebalance cortical excitability and restore compensatory striatal volume changes, increasing the functional connectivity of striato-cortico-cerebellar networks while also positively impacting neuroglia and neuroplasticity modification.

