## Summary and conclusions

This randomized double-blind sham-controlled crossover protocol study will investigate the neural and behavioral effects of iTBS over the bilateral M1 on idiopathic PD. The present combination of iTBS, cortical excitability measures, structural and functional neuroimaging data, and serum biomarkers represents a powerful approach that enables noninvasive, *in vivo* assessment and modulation of brain excitability, connectivity, and neuroprotection and neuroplasticity across motor and nonmotor brain networks in PD patients. We hypothesize that bilaterally stimulation of the M1 with excitatory iTBS will yield beneficial clinical effects that improve MDS-UPDRS-III scores in the ON medication state (i.e., motor improvement in PD patients) by modulating regionally specific changes in BG-cortical volume as well as by functional connectivity among the BG, cerebellum and cortical regions involved in motor processing. Moreover, we hypothesize that these functional and structural brain changes will be dynamically associated with the neuroprotective and neuroplasticity effects of real M1 iTBS reflected by stabilization of NfL and GFAP levels and by elevation of BDNF levels. Thus, these results may provide supportive evidence that the bilateral M1 is an optimal excitatory stimulation target for treatment among stable PD patients.

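### The trial is sized on MDS-UPDRS Part III alone, but Table 1 lists three unranked parts as primary and every test is to be adjusted, so 80% power for Part III is not secured as written

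*Protocol article*

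**What the plan says.** The protocol article describes the primary endpoint in two ways.

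- **Part III alone.** Under Recruitment and sample size: "The necessary sample size was calculated based on the primary endpoint, i.e., the motor clinical changes as assessed by the UPDRS-III score". The calculation uses two-sided 0.05 and 80% power and arrives at 21 subjects, with 24 to be enrolled. No allowance for multiplicity is mentioned. The hypothesis under Summary and conclusions is likewise that stimulation will "improve MDS-UPDRS-III scores in the ON medication state".
- **Three parts.** Table 1, under Primary outcomes, lists "MDS-UPDRS (part II, III, IV". It gives no order, composite or time point. The hypothesis at the end of the Discussion is motor improvement "as measured by MDS-UPDRS parts II, III, and IV".

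Two further statements bear on how these would be tested. Procedure and intervention schedules clinical evaluations at the last stimulation session, one week, two weeks and 28 days, the last visit "consisting of the fourth and final clinical evaluation". None is called primary. Statistical analysis sets the significance threshold at 0.05 only as an initial value and continues: "All statistical tests will be two-tailed and adjusted for multiple comparisons". It names no family of tests and no method, and it exempts no endpoint.

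**The concern.** The sample-size paragraph, Table 1 and the adjustment rule cannot all stand together with 80% power for Part III. If Table 1 defines the primary outcome and the adjustment applies to it, Part III is tested below 0.05 and 21 patients are too few for the effect that was planned for. If the sample-size paragraph defines it, Table 1 and the Discussion hypothesis are wrong.

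The primary result is the trial's main claim. While the part and the visit are open, a null result on Part III could reflect power that was never there. For a positive result, a reader could not tell from the protocol whether the part and visit reported were the ones intended.

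**Working it through.** **Inputs from the protocol article.** Evaluable number 21, enrolled 24, two-sided 0.05, power 80% (Recruitment and sample size). Three parts (Table 1). Four post-treatment evaluations per phase (Procedure and intervention). UPDRS-III in the sample-size paragraph is taken to be MDS-UPDRS Part III.

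**The plan's own figure.** The 21 cannot be reproduced, because the article gives neither an effect size nor a within-patient standard deviation. I solved for the standardised paired effect d that makes the stated design true and then held it fixed.

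For a 2 × 2 crossover with n evaluable patients and n − 2 degrees of freedom, power is the probability that a noncentral t with noncentrality d√n exceeds the two-sided critical value. Setting this to 80% at n = 21 and alpha 0.05 (critical value 2.093) gives d = 0.645 and noncentrality 2.954. As a check, the normal approximation gives d = (1.960 + 0.842)/√21 = 0.611.

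**Power for Part III with that effect, alpha divided by the number of tests (Bonferroni).** Noncentrality is 2.954 at n = 21 and 3.158 at n = 24.

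| Tests sharing 0.05 | Alpha per test | Critical t, n = 21 | Power, n = 21 | Power, n = 24 |
|---|---|---|---|---|
| 1 (as sized) | 0.05 | 2.093 | 80% | 85% |
| 3 parts | 0.0167 | 2.625 | 63% | 71% |
| 4 visits | 0.0125 | 2.759 | 58% | 67% |
| 3 × 4 = 12 | 0.0042 | 3.255 | 41% | 50% |

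The normal approximation is slightly kinder. At n = 21 it gives 66%, 62% and 47% for 3, 4 and 12 tests. For example, with three tests, 2.802 − 2.394 = 0.408, and the normal probability below 0.408 is 66%. At n = 24 with three tests it gives 73%.

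**A less conservative method.** Holm over the three parts at n = 21, by simulation, gives Part III about 64% power if only Part III responds. If all three parts respond equally, it gives 71% (correlation 0.8 between parts) to 74% (correlation 0).

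**Number needed.** To restore 80% for Part III at 0.05/3, 29 evaluable patients are needed. At the plan's 20% dropout that is 29/0.8 = 36.25, so 37 enrolled.

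**The case against.** The best reply is that the article already points to Part III. The sample-size paragraph speaks of a single primary endpoint and the Summary hypothesis names Part III. Testing order, adjustment method and analysis visit are commonly settled in a full protocol or analysis plan, neither of which is shown. Testing Part III first, at one visit, at the full 0.05 would keep the 80%. This stands as far as it goes: the loss is conditional, and the documents do not show that 80% has been lost. It does not remove the defect, because the article itself prints two different primary definitions and an adjustment rule without exception.

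A second reply is that success might mean a benefit on any one of the three parts. With equal effects on all three and Bonferroni, the chance of at least one significant part at n = 21 is about 95% at correlation 0 and 78% at correlation 0.8. The arithmetic is right, but no such rule is stated, and the 80% was claimed for Part III.

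A reader might also infer several stronger points that the documents do not support:

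- **That the stated primary outcome is 12 tests.** Table 1 names no visits, and the visit schedule does not say which parts are scored when. Twelve is a ceiling, and Bonferroni over correlated visits is its most pessimistic form.
- **That the plan inflates the false-positive rate.** Twelve independent tests at 0.05 would give 1 − 0.95¹² = 46%, but only if the commitment to adjust were broken and the tests were independent. It is not an error rate of this plan.
- **That Part IV will sit at its floor because of the criterion** "such as any dystonia and/or dyskinesia". Those are examples of incapacitating conditions that could interfere with carrying out the protocol. Nothing shows that every patient with motor complications is excluded, and no Part IV distribution is given.
- **That the abstract adds a third primary definition.** Its aim, that stimulation be "effective as an add-on treatment at reducing scores for both motor functional impairment and nonmotor symptoms in PD", is a goal and not an endpoint. Table 1 places the nonmotor scales under secondary outcomes.

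**Conclusion.** The point holds in conditional form. The sample-size paragraph and the Summary treat Part III as the one primary endpoint or hypothesis; Table 1 and the Discussion list three unranked parts; no visit is primary; and all tests are to be adjusted. As written, 80% power for Part III is not secured.

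The contradiction over the three parts is enough on its own: with Bonferroni over three, even full retention of all 24 patients leaves only 71% to 73%. The 41% is an outer bound and should be quoted only as such. All the figures assume that the planned effect is the one giving 80% at n = 21, and they depend on an adjustment method and family that the article does not name.

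**What to change.** Name MDS-UPDRS Part III, real versus sham, at one visit as the sole primary endpoint, tested at two-sided 0.05. Choose and justify the visit before unblinding; the documents do not single one out, and any of the four would remove the ambiguity. In Table 1, move Parts II and IV and the remaining visits to secondary. Bring the Discussion and Summary hypotheses and the abstract's goal into line. In Statistical analysis, state that the multiplicity adjustment applies to the secondary tests only.

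The alternative is to keep the three parts as primaries, state the family, method and success rule, and restate power at the adjusted alpha from a stated effect and standard deviation. Under the assumption used here, Bonferroni over three parts would need 29 evaluable patients.

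The first route is a change of wording. The article reports thirteen patients enrolled and four already crossed over, so it should be made and dated promptly. Its cost is that Parts II and IV and the other visits lose confirmatory status.
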